## Abstract

**Background:**

The immune system is essential for defending the body against pathogens and maintaining homeostasis. Recent global public health challenges have increased interest in natural products that enhance immune function. SH003, a compound derived from Astragalus membranaceus, Angelica gigas Radix, and Trichosanthis Radix, has shown potential as an immunomodulatory agent. This study aims to evaluate the efficacy and safety of SH003 in improving immune function in individuals with a mildly weakened immune systems.

**Methods:**

This randomized, double-blind, placebo-controlled trial will be conducted over 8 weeks with 120 participants aged 19 to 75 years who have experienced two or more upper respiratory infections in the past year. Participants will be randomly assigned to receive either SH003 or a placebo. The primary outcome is the change in natural killer cell activity. Secondary outcomes include cytokines levels (IL-2, IL-12, IFN-γ, TNF-α), inflammation markers (CRP, ESR), and stress and respiratory symptoms. Safety outcomes will be monitored through vital signs and laboratory tests.

**Discussion:**

This study represents the first clinical trial to evaluate the immune-enhancing effects of SH003 in a general population with mild immune system impairment. The results could offer valuable insights into the potential of SH003 as a novel immune support intervention.

**Trial registration:**

Clinical Research Information Service (registration number: KCT0009424, May 10, 2024, https://cris.nih.go.kr). Retrospectively registered.

## Background

Immunity, the defence system of body, is essential for recognizing and eliminating invading pathogens such as microbes, bacteria, viruses, as well as unnecessary internal tissues and by-products, thereby maintaining homeostasis [1]. Imbalances in this defence mechanism can lead to disease, highlighting the necessity for a well- regulated immune system to sustain health. Immune responses are broadly categorized into innate and adaptive immunity. The innate immune response, triggered within hours of pathogen entry, is mediated by host pattern recognition molecules and phagocytes equipped with Toll-like receptors [2]. In contrast, the adaptive immune response, though slower, strengthens immune reactions against the pathogen through memory response after initial defences are activated [3].

Recent environmental challenges, including fine dust and stressors, have heightened interest in immune-enhancing foods, particularly following public health crises like the MERS outbreak in 2015 and the COVID-19 pandemic [4]. Data from Statistic Korea in 2022 show that 46.5% of the population consumed health supplements primarily for disease prevention, with a significant portion planning to maintain or increase their intake [5]. The surge in health consciousness has spurred research into functional foods that enhance immune function and overall health.

Among the various natural compounds under study, Astragalus membranaceus is known in traditional medicine for its broad spectrum of health benefit, including its role in enhancing immunity and metabolic health [6–8]. Angelica Gigas Radix and Trichosanthis Radix are also notable for their medicinal properties, ranging from anti-inflammatory effects to enhancing metabolic and immune system functions [9–14].

SH003, a compound derived from these three plants, has been primarily studied for its anticancer properties with several preclinical study and clinical trials as an anticancer agent [15–17]. Recently, its potential to improve immune function was recognized following efficacy tests suggesting a new therapeutic avenue for SH003 in immunomodulation [18]. This study aims to conduct a randomized, double-blind, placebo-controlled trial to evaluate the effect of SH003 on human immune function, reflecting its potential as a novel immunostimulatory agent.

## Method/design

### Study design

This trial protocol (Version 1.1, approved on February 1, 2024) is designed as a single-center, randomized, double-blind clinical study to evaluate the efficacy and safety of SH003 in enhancing immune function over an 8-week period. This trial is a definitive, confirmatory study designed to evaluate clinical efficacy. The study has been approved by the Institutional Review Board of Jeonbuk National University Hospital in Republic of Korea and is structured and will be reported in accordance with Standard Protocol Items: Recommendations for Interventional Trials and Consolidated Standards of Reporting Trials guidelines [19, 20]. The study procedures are detailed in Table 1. Any important protocol modifications will be communicated to investigators during investigator meetings, and the final study design will be described in the resulting manuscript.

**Table 1 Tab1:**
[figure not shown]
Study schedule

## Participants

### Recruitment

Participants will be recruited through advertisements posted on the bulletin boards and websites of the clinical trial institution, as well as on relevant organizational websites.

#### Inclusion criteria

Adults aged 19 to 75 years at the time of screening.Individuals who have experienced two or more upper respiratory infections (such as the common cold, tonsillitis, pharyngitis, laryngitis, sinusitis, otitis media, and rhinitis) with in 12 months prior to screening.Individuals who have been fully informed about the clinical trial and have provided written informed consent to participate.

#### Exclusion criteria

Individuals with a WBC cound below 3000/µL or above 8000/µL at screening.Individuals who have received vaccinations (e.g., influenza, shingles, pneumococcal, COVID-19) within two months prior to the first intake of the investigational product.Individuals with a body mass index below 18.5 kg/m^2^ or above 35 kg/m^2^ at screening.Individuals taking hypertension medication.Individuals with thyroid disorders.Individuals undergoing treatment for or having uncontrolled diabetes (HbA1c > 7%).Individuals requiring treatment for clinically significant acute or chronic conditions affecting the cardiovascular, endocrine, immune, respiratory, hepatobiliary, renal and urinary, neuropsychiatric, musculoskeletal, inflammatory, hematological, oncological, or gastrointestinal systems.Individuals who have taken medications or health supplements related to immune function within one month prior to screening.Individuals with a history of significant hypersensitivity reactions to any component of the ingredients.Those who have undergone antipsychotic drug treatment within three months prior to screening.Individuals with a history or suspicion of alcohol or substance abuse.Those who have participated in another clinical trail within three months prior to screening.Individuals whose diagnostic laboratory tests show AST and ALT levels exceeding three times the upper reference limit or serum creatinine levels greater than 2.0 mg/dL.Pregnant of breastfeeding women.Women of childbearing potential not agreeing to use adequate contraception.Individuals deemed unsuitable for study participation by the principal investigator due to diagnostic laboratory results or other reasons.

### Randomization and allocation concealment

Eligible participants who meet the inclusion and exclusion criteria are randomly assigned to either the SH003 group or the placebo group. Randomization occurs after participants are confirmed eligible following their screening assessments. Participants are allocated in a 1:1 ratio to receive either the investigational drug or placebo, with the random sequence generated by the SAS 9.4 software for a total of 120 participants. An independent Contract Research Organization is responsible for generating the random allocation sequence. This sequence is then securely transmitted to the IP manufacturing facility. At this facility, each trial or placebo medication is produced according to the assigned random number and appropriately labeled to ensure blinding. Upon enrollment confirmation, participants are assigned their random numbers by the clinical research coordinator at the clinical trial site. This process ensures that both the participants and the clinical research team remain unaware of the allocation, thereby maintaining the integrity of the double-blinding method throughout the trial.

### Blinding

To maintain the integrity of the double-blind methodology in this study, the placebo used is indistinguishable from the IP in terms of shape, color, and scent. The labels for each unit of medication are applied at the manufacturing site before distribution to the clinical trial site. This procedure guarantees that neither the researcher nor the participants can identify whether a given treatment is the IP or the placebo, thus upholding the double-blinding throughout the duration of the trial. In the event of a serious adverse event that necessitates discussion regarding discontinuation of the study, unblinding may be permitted. In such cases, the unblinding procedure will be conducted through the contract research organization to ensure proper documentation and minimal bias. This will only occur when knowledge of the allocated intervention is essential for the safety of participant.

### Intervention

Participants will be randomly assigned to one of two groups upon their randomization, where they will receive a subject number. Over the course of 8 weeks, participants will orally ingest the investigational products twice daily following meals. SH003 group will take two tablets twice daily, once in the morning and once in the evening after meals, amounting to a total daily intake of 2 g of the active ingredient, SH003. Placebo group will also take two tablets twice daily, in the morning and evening after meals, but these capsules will not contain the active ingredient, amounting to a total daily intake of 0 g of SH003. During the trial period, the use of other medications or health supplements that may affect immune function will be prohibited.

### Investigational product and placebo production

The IP, designated as SH003, is composed of a 1:1:1 ratio of Astragalus membranaceus, Angelica gigas, and Trichosanthis Radix extracted with 30% ethanol. Each oblong, red tablet contains 500 mg of the active formulation. Excipients such as microcrystalline cellulose and lactose mixed powder are included in the composition. The placebo tablets are identically manufactured in oblong, red form using maltodextrin, microcrystalline cellulose, and lactose mixed powder, ensuring visual similarity to the IP in appearance. Both the IP and placebo are produced at Hanpoong Pharm & Foods Co Ltd, a facility compliant with Korea Good Manufacturing Practice standards.

### Medication compliance assessment

Medical compliance will be assessed during the third and fourth visits by examining the remaining quantities of the investigational products brought by participants. Participants are required to return any unused medication to the pharmacy, where it will be documented in the IP inventory and dispensing log. Compliance will be calculated using the following formula:$$\eqalign{& \>{\rm{Compliance}}\>\left( \% \right) = \cr & \,\,\,\,\,\,\,\,\,\,\,\,\,\,\,{\matrix{{\rm{number}}\>{\rm{of}}\> \hfill \cr {\rm{products}}\>{\rm{consumed}} \hfill \cr} \over \matrix{{\rm{number}}\>{\rm{of}}\>{\rm{products}}\>{\rm{that}}\> \hfill \cr {\rm{were}}\>{\rm{supposed}}\>{\rm{to}}\>{\rm{be}}\>{\rm{consumed}} \hfill \cr} } \times \>100 \cr} $$

### Outcome measure

#### Demographic and baseline information

Demographic information includes sex, age, alcohol consumption, smoking habits, medical and medication history, physical examination, and vital signs (blood pressure, pulse rate, body temperature), Anthropometric measurements include height, weight and body mass index.

### Primary outcome

The primary outcome will involve the isolation of cells using a natural killer cell (NK cell) isolation kit on hepain-treated venous blood, followed by the measurement of NK cell activity. The NK cell activity will be measured using the lactate dehydrogenase assay, with K562 (a human leukemia cell line) as the target cells. Effector to target cell ratios of 2.5:1, 5:1, and 10:1 will be employed. NK cell activity will be assessed using the CytoTox 96 W Non-Radioactive Cytotoxicity Assay Kit (Promega Co., WI, USA).

### Secondary outcomes

Secondary outcomes will include cytokines (IL-2, IL-12, IFN-γ, TNF-α), inflammatory markers (CRP, ESR), patient global assessment, and stress levels as measured by the Global Assessment of Recent Stress Scale. Additionally, the Wisconsin Upper Respiratory Symptom Survey-21 (WURSS-21) will be utilized.

### Safety outcomes

Safety outcomes will be assessed through monitoring of vital signs, hematological tests, biochemical tests, and urinalysis to ensure safety throughout the study. If serious adverse event occurs, or if an adverse event arises that leads the participants or investigator to decide to discontinue the intervention, the clinical trial will be terminated for that participants. All participants experiencing an adverse event will be followed up until resolution or stabilization. Any loss or harm caused by this clinical trial will be covered by insurance reimbursement.

### Sample size calculation

The study aims to evaluate the immune function effects of SH003 intake over 8 weeks, compared to a placebo. Since no prior studies have investigated the immune-modulating effects of SH003, the sample size calculation is based on data derived from other studies on natural products with immune-enhancing effects. The sample size calculation was based on a NK cell activity change of 5.62% in the SH003 group and 0.95% in the placebo group, with a standard deviation of 8.24% in the SH003 group and 8.05% in the placebo group [21]. To achieve a statistical power of 80% (β = 0.2) at a 5% significance level (α = 0.05), with a two-tailed test and an effect size of 4.67%, the required sample size was calculated. Assuming an equal allocation ratio (1:1) between the SH003 and placebo groups, and accounting for a 20% dropout rate, a total of 120 participants (60 per group) will be recruited for the study.

### Statistical analysis

Descriptive statistics will be presented for the primary efficacy variable (NK cell activity) and secondary efficacy variables (cytokines, WURSS-21, inflammation markers, patient global assessment (PGA), global assessment of recent stress scale) for each group. Between-group comparisons will be conducted using independent t-tests on changes from baseline to week 8, while within-group comparisons will be analyzed using paired t-tests. For repeated measurements of WURSS-21, comparisons will be made using repeated measures ANOVA or linear mixed models. Post-hoc analysis will be conducted for variables showing significant differences between groups. For PGA at week 8, frequencies and percentages will be presented by group, and between-group differences in improvement will be analyzed using the chi-square test or Fisher’s exact test. If normality assumptions are violated, appropriate data transformations (e.g., logarithmic transformation) will be applied, or non-parametric tests such as the Wilcoxon signed-rank test and Mann-Whitney U test will be used.

Data obtained from participants in this clinical trial will be analyzed across four populations: Safety, ITT (Intent-to-treat), FA (Full Analysis), and PP (Per Protocol). The Safety population includes participants who took at least one dose of the investigational product. The ITT population includes all participants who were assigned a study number. The FA population consists of participants who were randomized and have at least one post-baseline efficacy evaluation. The PP population includes those in the FA group who completed the trial without major protocol violations. Efficacy evaluations will primarily use the PP population, supplemented by ITT and FA analyses. Safety evaluations will be conducted using the Safety population.

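### The primary t-test on change in NK cell activity is valid, but adjusting for the baseline value already collected would usually give a more precise estimate at almost no cost

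*Protocol article*

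**What the plan says.** The abstract of the protocol article defines the endpoint: "The primary outcome is the change in natural killer cell activity". The Statistical analysis section fixes the test for this variable and for the continuous secondary variables: "Between-group comparisons will be conducted using independent t-tests on changes from baseline to week 8".

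No baseline covariate is named anywhere in the article. A model appears only for one secondary outcome: "For repeated measurements of WURSS-21, comparisons will be made using repeated measures ANOVA or linear mixed models". If normality fails, the plan transforms the data or turns to rank methods ("non-parametric tests such as the Wilcoxon signed-rank test and Mann-Whitney U test will be used"), again with no mention of baseline.

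The Sample size calculation section uses the same change-score scale. It assumes an "NK cell activity change of 5.62% in the SH003 group and 0.95% in the placebo group". The SDs entered for these changes are 8.24 and 8.05 percentage points, and the difference of 4.67 is tested two-sided at the 5% level. It allows for 20% dropout and arrives at 60 per group.

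**The concern.** Subtracting baseline and then applying a t-test assumes that a participant who starts one unit higher also ends one unit higher. If the true slope of week-8 on baseline differs from 1, the change score carries variation that a fitted slope would remove. A chance difference between the arms at baseline then also feeds into the estimated treatment effect.

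Baseline NK activity has to be measured in every analysed participant, because the outcome is its change. ANCOVA estimates the same treatment difference and costs one residual degree of freedom.

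The Study design section calls the trial definitive and confirmatory, so the precision of its single primary estimate matters. This is also a method the article states, not a detail it leaves open: an analysis plan with ANCOVA as primary would depart from this text.

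**Working it through.** **Inputs from the Sample size calculation section.** Difference 5.62 − 0.95 = 4.67; SDs of change 8.24 and 8.05; two-sided α 0.05; power 80%; 1:1 allocation; 20% dropout.

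**Inputs not in the article.** The correlation r between baseline and week-8 NK activity, and the SD at each visit. Both are assumptions below, and r is shown as a range.

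**Step 1: reproduce the stated sample size.**
- Pooled SD = √((8.24² + 8.05²)/2) = 8.146.
- n per arm = 2 × (1.960 + 0.842)² × 8.146² / 4.67² = 47.8, so 48.
- 48 / 0.80 = 60 per arm, 120 in total. The stated figure reproduces.
- Power of the t-test at 48 per arm is 80.2% by the normal approximation and 79.4% by the noncentral t. The second figure is the reference below.

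**Step 2: compare the variances.** Let s₀ and s₁ be the SDs at baseline and week 8.
- Variance of the change score: s₀² + s₁² − 2·r·s₀·s₁.
- ANCOVA residual variance: s₁²(1 − r²).
- Slope of week-8 on baseline: r·s₁/s₀.

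If s₀ = s₁ = s, these become 2s²(1 − r) and s²(1 − r²), so the ANCOVA variance is (1 + r)/2 of the change-score variance.

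**Step 3: equal SDs, 48 evaluable per arm.** The SD of change stays at 8.146 and is multiplied by √((1 + r)/2). Power is by noncentral t with 93 degrees of freedom for ANCOVA and 94 for the t-test.

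| Assumed r | Variance ratio | Effective SD | Power | 95% CI half-width |
|---|---|---|---|---|
| t-test on change | 1 | 8.15 | 79.4% | 3.30 |
| 0.3 | 0.65 | 6.57 | 93.2% | 2.66 |
| 0.5 | 0.75 | 7.05 | 89.4% | 2.86 |
| 0.7 | 0.85 | 7.51 | 85.4% | 3.04 |
| 0.8 | 0.90 | 7.73 | 83.4% | 3.13 |
| 0.9 | 0.95 | 7.94 | 81.4% | 3.22 |

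A simulation of 20,000 trials per setting agrees. Change score against ANCOVA, power was 79.3 and 92.7% at r = 0.3, 79.6 and 89.2% at 0.5, 79.5 and 85.4% at 0.7, and 79.3 and 81.2% at 0.9. Type I error was about 5% for both methods.

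**Step 4: unequal SDs.**
- s₁ = 1.25·s₀ and r = 0.8: the slope is 0.8 × 1.25 = 1, the ratio is 1.00, and there is no gain (79.4%).
- s₁ = 1.2·s₀ and r = 0.7: the ratio is 1.44 × 0.51 / (1 + 1.44 − 1.68) = 0.7344/0.76 = 0.97, and power is 80.7%.
- s₁ = 0.8·s₀ and r = 0.7: the ratio is 0.64 × 0.51 / (1 + 0.64 − 1.12) = 0.3264/0.52 = 0.63, a larger gain than the 0.85 under equal SDs.

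**Step 5: chance imbalance, equal SDs.** At 48 per arm the standard error of the baseline difference is √(2/48) ≈ 0.2 SD. An imbalance of that ordinary size shifts the change-score estimate by (1 − r) × 0.2 × s, where s = 8.146/√(2(1 − r)).
- r = 0.3: 0.7 × 0.2 × 6.88 = 0.96 points.
- r = 0.5: 0.5 × 0.2 × 8.15 = 0.81 points.
- r = 0.7: 0.3 × 0.2 × 10.52 = 0.63 points.

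These are about 21%, 17% and 14% of the 4.67 design difference, in either direction.

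**The case against.** The strongest reply is that nothing here is wrong. The endpoint is a change, the sample size is built on SDs of change, and the test compares changes, so the three agree. Under 1:1 randomisation the t-test is unbiased and keeps its error rate. This stands in full: the point concerns efficiency, and a reader should not infer that the planned result would be biased or invalid.

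The second reply is that the size of the gain rests on figures the article does not give. This also stands. A reader might infer that subtraction over-corrects whenever r is below 1. That holds only for equal SDs: the relevant slope is r·s₁/s₀, which can reach or exceed 1 when the week-8 SD is larger. The article gives neither SD, so the general statement is unsupported.

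A reader might also infer that the trial has no reserve at all. The 48 per arm is what remains if the whole dropout allowance is used. With 10% loss, 54 per arm remain and the planned t-test has 83.9% power.

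Finally, the wide age range and the absence of any mention of stratification might suggest that age and sex must be covariates. Nothing in the article says that either predicts NK activity, and none of the computed gain comes from them.

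What does not stand is the suggestion that the choice is neutral. Under 1:1 allocation ANCOVA is asymptotically never less precise than the change score, and it needs no additional data.

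**Conclusion.** The point holds as a recommended improvement in precision, not as a correction of an error. The direction is secure. The size is conditional: with equal SDs at both visits and 48 evaluable per arm, the gain runs from about 14 power points at r = 0.3 to about 2 at r = 0.9. It can fall to nothing if the slope happens to be 1, and can exceed these figures if the week-8 SD is below the baseline SD. Adjustment also removes the shift that a chance difference in baseline NK activity would otherwise put into the estimate.

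**What to change.** Before unblinding, state the primary analysis as an ANCOVA of week-8 NK cell activity (or of its change, which gives the same treatment estimate) on treatment and baseline NK cell activity. Report the adjusted difference with its 95% CI. Keep the independent t-test on change as a supportive analysis.

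Use the same baseline adjustment for the continuous secondary outcomes now compared by t-test: the cytokines, CRP, ESR and the stress scale. Where the plan's non-normality rule calls for a transformation, put both the outcome and its baseline on the log scale. The text should say how the adjusted model and that rule fit together.

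Leave the sample size of 120 unchanged; it was derived for the less precise test. Age and sex are optional covariates and not part of this change.

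The cost is a sentence for the primary analysis, a little more text for the secondary outcomes, and one residual degree of freedom (93 instead of 94 at 48 per arm). No new data are needed.

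### The primary test and effect measure for NK cell activity hang on an undefined normality check, although only the difference in mean change was sized

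*Protocol article*

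**What the plan says.** In the protocol article, Statistical analysis, the comparison of the groups is set out as follows: "Between-group comparisons will be conducted using independent t-tests on changes from baseline to week 8". This covers the primary variable, NK cell activity, as well as the secondary ones. The same paragraph then provides a way out: "If normality assumptions are violated, appropriate data transformations (e.g., logarithmic transformation) will be applied, or non-parametric tests", with the Wilcoxon signed-rank and Mann-Whitney tests as the examples of the latter.

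The Sample size calculation section starts from this assumption: "NK cell activity change of 5.62% in the SH003 group and 0.95% in the placebo group". For the spread of those changes it takes SDs of 8.24 (SH003) and 8.05 (placebo), and it sizes a two-sided comparison for a difference of 4.67. The Study design section describes the trial as definitive and confirmatory.

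**The concern.** The sentence is a rule, but an open one. Three things are left undecided:

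- how a violation of normality is recognised;
- whether a transformation or a rank test then takes precedence;
- whether a transformation applies to the change or to the values from which the change is formed.

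The permitted routes do not estimate the same thing. A t-test on change estimates a difference in mean change. A log of the raw values leads to a ratio of geometric means. Mann-Whitney compares the groups by rank. Only the first corresponds to the 4.67 for which the trial was sized.

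The one transformation named also fits badly with the variable named. Changes can be negative, and a negative number has no logarithm.

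At stake is whether a confirmatory trial has one primary result fixed in advance. A reader of the final report could not tell whether the scale of the NK effect was planned or chosen after the data were inspected.

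**Working it through.** **Inputs** (protocol article, Sample size calculation): mean change 5.62 (SH003) and 0.95 (placebo); SD of change 8.24 and 8.05; two-sided alpha 0.05; power 80%; 1:1 allocation; 20% dropout; 120 in total.

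**1. The plan's own figure.**
- Difference = 5.62 − 0.95 = 4.67.
- Pooled SD = √[(8.24² + 8.05²)/2] = √66.35 = 8.146.
- n per group = 2 × (1.960 + 0.842)² × 66.35 / 4.67² ≈ 47.8, rounded up to 48.
- With dropout: 48 / (1 − 0.20) = 60 per group, 120 in total.

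The stated size reproduces under the normal approximation, so the inputs can be taken as they stand. It also confirms that what was sized is a difference in mean change on the original scale.

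**2. Can the change be logged?** Assume normal changes with these means and SDs. The share below zero is Φ(−mean/SD):
- SH003: Φ(−5.62/8.24) = Φ(−0.682) = 24.8%.
- Placebo: Φ(−0.95/8.05) = Φ(−0.118) = 45.3%.
- Average at 1:1: (24.8 + 45.3)/2 = 35.0%, about 42 of 120 participants.

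The chance that all 96 completers have a positive change is (1 − 0.248)⁴⁸ × (1 − 0.453)⁴⁸ ≈ 3 × 10⁻¹⁹. The log of the change is therefore not available. The log of positive raw values is.

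**3. What each permitted route estimates.**

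| Route | Effect measure | Matches the sized 4.67? |
|---|---|---|
| t-test on change | difference in mean change | yes |
| log of baseline and week-8 values | ratio of geometric means | no |
| Mann-Whitney | comparison by rank | no |

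**4. Cost in type I error.** These are null simulations with 48 per group. A Shapiro test stands in for the normality check, which is an assumption because the protocol names none.

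*Fixed switch, t-test to Mann-Whitney* (4,000 runs; normal, t with 3 df and lognormal data): 4.2 to 5.0%. For normal data at an SD of 8.1, close to the sizing assumption, the result was 5.0%.

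*Skewed marker* (6,000 runs; lognormal, correlation 0.6 between visits):

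| Rule | log-SD 0.8 | log-SD 0.4 |
|---|---|---|
| Fixed switch to log scale | 4.9% | 4.7% |
| Fixed switch to Mann-Whitney | 5.0% | 4.8% |
| Better of log and Mann-Whitney, only after a violation | 6.8% | 5.5% |

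A second run of the last row gave 6.9% and 5.7%. The Monte Carlo standard error near 5% is √(0.05 × 0.95/6000) ≈ 0.3 percentage points, so the fixed switches cannot be told apart from 5%. The t-test on change alone also stayed at or slightly below 5% with the skewed marker, so the switch is not needed to protect its error rate at this sample size.

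**The case against.** **The log is not impossible.** The protocol speaks of appropriate transformations, gives the log only as an example and does not say that the change is what would be logged. The sentence covers cytokines and CRP, for which logging the raw values is usual and feasible. A non-parametric test also remains. This stands. A reader might infer that the plan prescribes an analysis that cannot be run; the text does not support that. What remains is that the object of the transformation is unstated, and that the feasible reading changes the effect measure.

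**The 5% level is not lost.** A reader might infer that any data-dependent choice of test breaks the stated level, perhaps to about 8%. Taking the best of the t-test, the log-scale test and Mann-Whitney does give 7.0 to 8.5% in the skewed marker. But that ignores the normality condition, and the protocol opens the alternatives only after a violation. A fixed switch holds about 5%. Inflation needs selection between remedies on their p-values, and then it is modest. This objection stands too.

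**The evidence is indirect.** The 25% and 45% assume normal changes, the case in which a switch would seldom be triggered. The skewed simulation is not NK data, for which no distribution is given. Both points are fair and limit the figures. Neither makes the rule less open.

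**This belongs in the statistical analysis plan.** A normality criterion and the order of fallbacks often sit there, and their absence alone would be no finding. But the article does not stay silent: it states a rule for the primary outcome, and that rule leaves the test and effect measure open. A separate plan may narrow it; the text as written does not.

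**ANCOVA is a preference.** The t-test on change is valid under randomisation, and pre-setting it would also cure the defect. Hence ANCOVA is recommended below rather than required.

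**Conclusion.** The point holds in this form: for a trial called confirmatory, the primary test and effect measure for NK cell activity depend on an undefined check, with an open choice between remedies, and only one of the possible measures was sized.

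The log cannot be taken of the change scores, given about 25% (SH003) and 45% (placebo) negative changes under normality. It can be taken of positive raw values, at the price of a ratio that was not sized.

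The effect on type I error is small: about 5% for a fixed switch, and about 5.5 to 7% if the better remedy is picked after a violation. The latter range rests on an assumed lognormal marker and an assumed Shapiro trigger. The larger harm is to interpretation, because the primary result has no single scale fixed in advance. The wording should be changed; the sample size is not affected.

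**What to change.** - **NK cell activity:** remove the normality-triggered switch. Pre-set one primary analysis on the original scale, whatever the distribution. Preferably this is ANCOVA of the week-8 value or of the change, adjusted for the baseline value that is already collected. It still reports a difference in means, the quantity that was sized. Name a rank-based test as a sensitivity analysis.
- **Cytokines, CRP and ESR:** state in advance that logs apply to the baseline and week-8 values, not to the change, and that results are reported as ratios of geometric means.

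This is a change of wording only, with no added participants, visits or assays. The sponsor gives up the freedom to choose the test later.

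### The per-protocol set is the primary efficacy population in a confirmatory test of difference from placebo, so the headline result is not fully protected by randomisation

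*Protocol article*

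**What the plan says.** The Statistical analysis section of the protocol article defines four sets: Safety, ITT (everyone assigned a study number), FA (randomised, with at least one efficacy evaluation after baseline) and PP. It ranks them for efficacy: "Efficacy evaluations will primarily use the PP population, supplemented by ITT and FA analyses". It defines the PP set as follows: "The PP population includes those in the FA group who completed the trial without major protocol violations". The between-group test is an independent t-test on change from baseline to week 8.

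Three other sections bear on this choice:

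- **Study design** describes the trial as definitive and confirmatory.
- **Sample size calculation** plans "with a two-tailed test and an effect size of 4.67" percentage points and states no non-inferiority margin. It arrives at the total by "accounting for a 20% dropout rate, a total of 120 participants (60 per group) will be recruited for the study".
- **Safety outcomes** ends the trial for a participant after a serious adverse event, or after an adverse event that leads the participant or investigator to stop the intervention. Such a participant does not complete and so is not in the PP set.

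**The concern.** This is a stated choice, not a detail left open. If the PP and ITT results disagree, the wording lets PP decide.

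In a test of difference from placebo, the validity of the 5% level comes from comparing the groups as randomised. Completion and freedom from major violations are observed later. If SH003 and placebo differ in tolerability, PP removes different kinds of participant from each arm, and those retained need no longer be comparable. Blinding limits biased judgement about who counts as a violator, but it does not prevent selection through tolerability. At stake is the one primary conclusion of the trial, on change in NK cell activity.

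**Working it through.** **1. Reproduce the planned sample size.** Inputs from Sample size calculation: "a NK cell activity change of 5.62% in the SH003 group and 0.95% in the placebo group", so the difference is 5.62 − 0.95 = 4.67 points; SDs 8.24 and 8.05; two-sided α 0.05; power 80%; allocation 1:1; dropout 20%.

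- n per arm = (1.960 + 0.842)² × (8.24² + 8.05²) / 4.67² = 47.76, so 48.
- 48 / (1 − 0.20) = 60 per arm, 120 in total. This matches the protocol exactly.
- Pooled SD = √[(8.24² + 8.05²)/2] = 8.146.

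**2. What selection can do to type I error.** The documents give no exclusion rates, so these values are assumptions: 20% of SH003 and 10% of placebo participants fall outside PP, their mean change is 8 points (about 1 SD) below that of those retained, and there is no true effect.

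- If a fraction p is excluded, the mean of those retained lies 8p above the mean of the whole arm.
- SH003: 8 × 0.20 = 1.6. Placebo: 8 × 0.10 = 0.8. Bias = 1.6 − 0.8 = +0.8 points, which is 0.8/4.67 = 17% of the planned difference.
- Analysed: 60 × 0.80 = 48 and 60 × 0.90 = 54. Standard error = 8.146 × √(1/48 + 1/54) = 1.616. Noncentrality = 0.8/1.616 = 0.495.
- The exact two-sided t-test (100 df) rejects in 7.8% of trials: 7.1% in favour of SH003 and 0.7% in favour of placebo. The nominal figure is 2.5% each way.

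Swapping the two exclusion rates gives a bias of −0.8 points and the same 7.8%, now mostly against SH003. Equal rates with equal deficits give no bias. A second assumed case, a bias of 1 point with 48 per arm, gives 9.1%.

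**3. Does the 20% allowance hold for a PP analysis?** The exact power for 4.67 points, with the normal approximation alongside, is:

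| Total loss from PP | Per arm | Exact t | Normal approximation |
|---|---|---|---|
| 20% | 48 | 79.4% | 80.2% |
| 25% | 45 | 76.7% | 77.6% |
| 30% | 42 | 73.8% | 74.8% |

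At 20% total loss the planned power is met to within a point. There is no slack beyond that. Losses above 20% are assumptions.

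**4. Power if ITT is primary.** The exact power with all 60 per arm analysed, dilution values assumed, is:

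| Effect | Difference | Power |
|---|---|---|
| Full | 4.67 | 87.6% |
| Diluted 10% | 4.67 × 0.9 = 4.20 | 80.0% |
| Diluted 20% | 4.67 × 0.8 = 3.74 | 70.3% |

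**The case against.** Several points can fairly be made for the plan.

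**ITT and FA results are planned anyway.** This is true, and a reader could compare them with PP. PP is also a subset of randomised participants, so it would be too strong to say that it is no randomised comparison at all. But the protocol makes the other sets supplementary, so they do not decide the conclusion.

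**The sample size suits a PP analysis.** This also stands. Inflating by 1/(1 − 0.20) leaves exactly the 48 per arm that the calculation needs. A reader might infer that the allowance fails because it names dropout only, while PP also removes major violators. That follows only if the two together exceed 20%, and the article gives no violation rate. In the illustration above (48 and 54 analysed), power is about 82%.

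**The direction of bias is unknown.** A reader might assume that PP favours SH003. The documents do not support that: the sign depends on which arm loses more participants and how those lost differ from those kept.

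**Infections do not supply an exclusion rate.** Participants enter with recurrent respiratory infections, and under Intervention "the use of other medications or health supplements that may affect immune function will be prohibited". It is tempting to turn the entry rate into a PP loss: 2 × 8/52 = 0.31 expected infections, so about 26% of participants with at least one. That is an infection rate. Exclusion would further require taking a medicine, its being of the prohibited kind, and its counting as a major violation, a term that the article does not define. With no true effect, infections would also be balanced between arms and would not by themselves create bias.

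**Missing-data rules may be elsewhere.** The t-test on change needs a week-8 value, but how missing values are handled is commonly left to the full protocol or SAP. Its absence from the article is not a fault.

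**Conclusion.** The point holds for the choice of primary population. In a self-declared confirmatory test of difference from placebo, the deciding analysis is conditioned on events after randomisation that treatment can affect. The article itself supplies one route, adverse-event discontinuation. The 5% error rate is therefore not assured for the headline result.

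The size cannot be fixed from the documents. The +0.8 points and 7.8% rest on assumed exclusion rates (20% and 10%) and an assumed 8-point deficit. They show that moderate imbalance matters, not what will happen.

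On power, only a note of caution is justified. The 20% allowance keeps about 80% power for a PP analysis as long as dropouts and major-violation exclusions together stay within 20%. No shortfall is shown.

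**What to change.** In Statistical analysis, replace the sentence that ranks the populations with: *The primary efficacy analysis includes all randomised participants in the arm assigned (ITT); FA and PP analyses are supportive.* Participants without a week-8 NK value should stay in the primary analysis by a method set out in the full protocol or SAP. To be credible, the change has to be made before unblinding.

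The cost is one sentence and some programming; the planned 120 need not change for this reason alone. The real downside is dilution by participants who stop or deviate. Power stays at 80.0% with 10% dilution but falls to 70.3% with 20%, and imputing missing values does not restore the full information of 60 per arm. That trade-off should be accepted knowingly. If PP were kept as primary, Sample size calculation should at least say whether the 20% covers major-violation exclusions as well as dropout.
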